#### Demographics and baseline characteristics

2.6.1

Age (years), sex (male/female), BMI (kg/m^2^), smoking history (yes/no; defined as continuous or cumulative smoking for more than six months), alcohol consumption (yes/no; defined as drinking ≥1 time per month for ≥1 year), and NYHA functional class (I: patient has heart disease but no limitation of physical activity; ordinary physical activity does not cause undue fatigue, palpitations, dyspnea, or angina; II: slight limitation of physical activity due to heart disease; III: marked limitation of physical activity due to heart disease; IV: heart disease with symptoms of heart failure or angina at rest, any physical activity increases discomfort).

#### Preoperative comorbidities

2.6.2

Hypertension (systolic BP ≥140 mmHg or diastolic BP ≥90 mmHg or taking antihypertensive drugs, yes/no), diabetes (fasting glucose ≥7.0 mmol/L, 2-hour postprandial glucose ≥11.1 mmol/L, random glucose ≥11.1 mmol/L, or taking antidiabetic drugs, yes/no), arrhythmias (including atrial arrhythmia, ventricular arrhythmia, atrioventricular block, yes/no), history of cerebrovascular disease (including cerebral infarction or hemorrhage, yes/no), hypoproteinemia (serum total protein <60 g/L or serum albumin <35 g/L, yes/no), pulmonary comorbidities (including chronic obstructive pulmonary disease, asthma, interstitial lung disease, pulmonary edema, yes/no), anemia (adult male <120 g/L, adult female <110 g/L, yes/no) and obesity (BMI ≥30 kg/m^2^, yes/no).

#### Preoperative laboratory and functional indicators

2.6.3

Lactate level (mmol/L), platelet count (10⁹/L), hemoglobin (g/L), lymphocyte count (10⁹/L), neutrophil count (10⁹/L), monocyte count (10⁹/L), B-type natriuretic peptide (BNP, pg/mL), C-reactive protein (CRP, mg/L), left ventricular ejection fraction (LvEF, %), cardiac troponin I (CTnI, μg/L), myoglobin (Mb, μg/L), total bilirubin (*μ*mol/L), serum creatinine (μmol/L), alanine aminotransferase (U/L), aspartate aminotransferase (U/L), blood urea nitrogen (mmol/L), and preoperative blood glucose (mmol/L) within seven days before surgery.

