#### Inclusion criteria

2.2.1

Age ≥18 years; 2. Patients undergoing elective open cardiac surgery with CPB, such as coronary artery bypass grafting, valve replacement or repair, artificial vascular replacement, cardiac tumor resection, other, and combined surgery, such as valve replacement combined with coronary artery bypass grafting.

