#### Exclusion criteria

2.2.2

History of previous cardiac surgery requiring sternotomy and/or CPB; 2. Emergency surgery; 3. Presence of any type of preoperative infection (e.g., preoperative pneumonia, infective endocarditis); 4. Severe hepatic or renal dysfunction (e.g., jaundice, coagulation disorders, hepatic encephalopathy, serum creatinine >442 μmol/L, blood urea nitrogen >20 mmol/L, or requiring dialysis); 5. Preexisting immunodeficiency disorders (e.g., HIV infection, use of immunosuppressive drugs, autoimmune diseases).

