### Exposure

2.4

Trained research personnel will measure patients' blood lactate levels during cardiopulmonary bypass using Radiometer ABL90 FLEX blood gas analyzer. The procedures are as follows:
During cardiopulmonary bypass, arterial blood samples will be collected from the radial or femoral artery at the following time points: T_1_, after the initiation of cardiopulmonary bypass, when coronary perfusion with cardioplegic solution induces cardiac arrest; T_2_, T_3_, …, Tn, every 1 h after the start of bypass; T_n_ _+_ _1_, 10–20 min before the end of bypass; and T_n_ _+_ _2_, within 5 min after the end of bypass. Here, T_n_ represents the last full-hour sampling point during bypass. Additionally, extra samples will be collected whenever there is a sudden increase in lactate during CPB (e.g., following hypotension or hypoperfusion events). At least four lactate measurements during cardiopulmonary bypass are required for TWA lactate calculation.Within 1 min of blood collection, lactate levels will be measured using the blood gas analyzer and recorded in mmol/L to one decimal place. If duplicate measurements are performed at the same time point, the mean value will be used as the final lactate measurement.The time-weighted average lactate (TWA) will be calculated from the lactate values obtained at different time points. TWA is defined as the area under the curve of lactate levels over time divided by the total observation interval, using the formula:$$TWA=\frac{1}{T}\overset{n=1}{\underset{i=1}{\sum }}\;\left(\frac{v_{i}+v_{i+1}}{2}\right)\Delta t_{i}$$Evidence from previous cardiac surgery cohort studies has reported that lactate concentration of >2.0 mmol/L during surgery or in the early postoperative period are already associated with increased postoperative morbidity and mortality. Accordingly, based on the available evidence, recommendations from international sepsis guidelines, TWA lactate of 2.0 mmol/L is selected as the prespecified cutoff for exposure classification. TWA lactate ≥2.0 mmol/L during CPB will be categorized into the exposure group, with the TWA lactate <2.0 mmol/L classified into the non-exposure group (24–27). Lactate will also be analyzed as a continuous variable in the subsequent analyses.We will also calculate the following lactate indices to comprehensively characterize lactate exposure:

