### Covariates

2.6

To ensure appropriate confounder control and strengthen inference, a directed acyclic graph (DAG) and temporal sequence diagrams for variables were constructed based on prior clinical knowledge and published evidence (Figures 3, 4). These diagrams clarify the assumed causal pathways linking intraoperative TWA lactate to postoperative infection. The DAG identified the following minimal sufficient adjustment set: age, sex, BMI, lifestyles (including smoking and alcohol consumption), comorbidities, preoperative lactate, anesthesia factors, surgery and CPB factors (including surgery type, operation duration, CPB time, aortic cross-clamp time, and intraoperative body temperature). These variables are common causes of elevated lactate during cardiopulmonary bypass and of postoperative infection risk. Mediators include hepatic and renal dysfunction, lactate clearance, inflammatory response, and immunosuppression. ICU length of stay, hospital length of stay, time to extubation, and mortality are considered collider variables.

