**Figure 4 F4:**
[figure not shown]
Directed acyclic graph (DAG) illustrating the assumed causal structure between intraoperative TWA lactate (exposure) and postoperative infection (outcome). The exposure is represented by a green node with a triangle symbol. The outcome, postoperative infection, is shown as a blue node with a thick black vertical line. Other variables are represented as follows: blue nodes depict ancestors of the outcome, namely mediators; red nodes represent ancestors of both the exposure and outcome; pale grey nodes signify unobserved or latent variables; and darker grey nodes represent colliders. The definitions of TWA lactate and postoperative infection have been elaborated in the Methods section. Mediators located on the causal pathway between exposure and outcome, as well as colliders jointly caused by both exposure and outcome, will not be adjusted for to avoid overadjustment bias. The minimal adjustment set for this model is age, sex, BMI, lifestyle, comorbidities, preoperative lactate, anesthesia factors, and surgery and CPB factors.

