After local infiltration with 10 mg lidocaine above the left radial artery, the radial artery is cannulated for invasive arterial blood pressure monitoring. Anesthesia induction is performed with the patient in a head-up ramp position: inhalation of pure oxygen at 6 L/min via mask, followed by slow intravenous injection of 0.4 μg/kg sufentanil citrate. After 3 min, 0.3 mg/kg etomidate is administered. Upon loss of consciousness (MOAA/S score of 0), 0.2 mg/kg cisatracurium is given, and endotracheal intubation is performed when the train-of-four count reaches 0. The tube is secured at the right corner of the mouth, and mechanical ventilation is initiated. Arterial blood gas is measured 5 min after intubation, adjusting tidal volume to maintain PaO_2_ 100–200 mmHg and PCO_2_ 35–45 mmHg based on the P_ET_CO_2_–PaCO_2_ gradient. Anesthesia is maintained with propofol 2 mg/kg·h, dexmedetomidine 0.5 μg/kg·h, cisatracurium 0.15 mg/kg·h, and inhaled 1% sevoflurane. Nasopharyngeal and rectal temperature probes and a urinary catheter are placed. Central venous catheterization is performed in a head-left, Trendelenburg position (<45° tilt) for pressure monitoring.

During skin incision, sternotomy, aortic manipulation such as side-wall clamping or aortic cannulation, CPB initiation, rewarming, hemostasis, and sternal wire closure, sufentanil 0.05–0.1 μg/kg is administered. Arterial pressure is maintained at 80–100 mmHg before arterial cannulation for CPB. Heparin 3 mg/kg is given, and ACT is measured 5 min later; arterial cannulation proceeds when the average ACT ≥360 s, and CPB starts when ACT ≥480 s. After CPB initiation, intravenous fluids are stopped or limited to anesthetic maintenance drugs, and CVP is reduced to near 0 or negative. Ventilation is paused after superior and inferior vena cava clamping, and the expiratory valve is set at 5–10 cmH_2_O for static lung inflation. Rewarming during CPB is performed with vasopressor infusion to achieve effective drug concentration before CPB reduction and reperfusion; low-weight or malnourished patients are rewarmed slowly to nasopharyngeal temperature ≥37.0 °C and rectal or bladder temperature ≥36.5 °C before CPB termination, with active warming to prevent hypothermia-induced coagulopathy.

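### The baseline lactate used for adjustment may be up to seven days old and no value shortly before bypass is named, so control for pre-bypass lactate is only partial

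*Protocol article*

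**What the plan says.** - **Adjustment set.** Section 2.6 lists "comorbidities, preoperative lactate, anesthesia factors, surgery and CPB factors" among the variables to be adjusted for, and the Figure 4 legend repeats it: "The minimal adjustment set for this model is age, sex, BMI, lifestyle, comorbidities, preoperative lactate, anesthesia factors, and surgery and CPB factors". Section 2.9 applies this set in the primary logistic model.
- **Timing of the baseline.** Section 2.6.3 opens its list with lactate and closes it with "blood urea nitrogen (mmol/L), and preoperative blood glucose (mmol/L) within seven days before surgery". Read over the whole list, the window allows a lactate up to seven days old. Read as governing glucose only, it leaves lactate with no window.
- **Exposure.** Under section 2.4, "TWA lactate ≥2.0 mmol/L during CPB will be categorized into the exposure group". This is an absolute level, not a change from baseline. The first scheduled sample comes "after the initiation of cardiopulmonary bypass, when coronary perfusion with cardioplegic solution induces cardiac arrest", so no exposure sample shows the level at bypass entry.
- **An earlier gas exists.** Section 2.7 states: "Arterial blood gas is measured 5 min after intubation". No section names its lactate as the baseline covariate.
- **Sensitivity analyses of exposure.** Section 2.9 uses lactate load and peak lactate during bypass, which are also absolute levels.

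**The concern.** The authors treat preoperative lactate as a common cause of TWA lactate and infection. Its role in the model is to separate what the patient brought to bypass from what arose there. The protocol samples lactate hourly on bypass, adds samples for sudden rises, and calls lactate dynamic among its limitations. A value several days old fits poorly with that premise.

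Suppose a patient enters bypass with raised lactate and stays there, while the model holds a normal value from days earlier. Part of the risk that goes with the pre-bypass state is then credited to lactate on bypass. The Discussion aims at an independent association and looks ahead to intraoperative management and to trials of lowering lactate. Those uses depend on the separation.

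**Working it through.** **The plan's own figures.** The documents give no figure for this point: no correlation between an older lactate and the pre-bypass value, no correlation of pre-bypass lactate with TWA, and no odds ratio for pre-bypass lactate. The only related figure is the sample size. From 10.4% and an odds ratio of 2.75, the odds are 2.75 × 0.104/0.896 = 0.319, so the exposed rate is 0.319/1.319 = 24.2%. The pooled two-proportion formula at two-sided 0.05 and 90% power then gives 156 per group, as stated. This point does not change it.

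**Assumed inputs for an illustration.**
- B: true log lactate just before bypass, standardised.
- W: recorded baseline, with correlation r to B.
- TWA: log scale, with correlation ρ to B (0.4 or 0.6), split at its median into exposed and unexposed.
- Infection depends on B only, with odds ratio OR_B per SD (1.2, 1.5 or 2.0) and intercept −2.1, which gives 11% to 13% infected. Bypass lactate has no effect, so the correct adjusted odds ratio is 1.
- No other covariate is in the model.

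**Approximate formula.** Regress B linearly on the exposure indicator and W, with k = √(2/π) = 0.798:

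ln(spurious OR) ≈ ln(OR_B) × 2kρ(1 − r²) / (1 − k²ρ²r²)

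Example with OR_B = 1.5, ρ = 0.6, r = 0.5:
- 2kρ = 2 × 0.798 × 0.6 = 0.957; times (1 − 0.25) = 0.718.
- Denominator: 1 − 0.637 × 0.36 × 0.25 = 0.943; ratio = 0.762.
- 0.405 × 0.762 = 0.309, so the spurious OR is about 1.36.
- With a worthless baseline (r = 0): 0.405 × 0.957 = 0.388, or about 1.47.

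Adjustment at r = 0.5 thus removes 1 − 0.309/0.388 = 20% of the bias on the log scale. At r = 0.8 the ratio is 0.957 × 0.36/0.853 = 0.404, the log OR is 0.164, and 58% is removed.

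**Simulation** (1,000,000 patients per cell; 95% Monte Carlo error about 0.01 on the log scale). Spurious adjusted odds ratio for the exposed group:

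| ρ | OR_B | r = 0 | 0.2 | 0.6 | 0.8 | 0.9 | 1.0 |
|---|---|---|---|---|---|---|---|
| 0.4 | 1.2 | 1.12 | 1.11 | 1.09 | 1.04 | 1.02 | 0.99 |
| 0.4 | 1.5 | 1.28 | 1.28 | 1.19 | 1.11 | 1.06 | 1.00 |
| 0.4 | 2.0 | 1.53 | 1.49 | 1.33 | 1.18 | 1.09 | 1.00 |
| 0.6 | 1.2 | 1.17 | 1.17 | 1.14 | 1.08 | 1.05 | 0.99 |
| 0.6 | 1.5 | 1.48 | 1.45 | 1.30 | 1.19 | 1.09 | 0.99 |
| 0.6 | 2.0 | 1.90 | 1.84 | 1.58 | 1.32 | 1.18 | 0.99 |

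**Reading the table.**
- For r from 0.2 to 0.8 the corners are 1.04 and 1.84, so roughly 1.05 to 1.85.
- Against the design odds ratio of 2.75 (ln = 1.012), 1.84 is 0.610/1.012 = 60% of the log effect and 1.04 is 0.039/1.012 = 4%.
- Only r = 1, a perfect measure of lactate at bypass entry, returns 1. If a post-intubation sample reaches r = 0.8 to 0.9, the table leaves 1.02 to 1.32.

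**The case against.** **The plan already adjusts for the confounder.** This is correct. A reader might infer that the adjustment cannot separate patients whose lactate was raised before bypass. The table does not support that: control is partial, and it fails wholly only at r = 0.

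**Eligibility.** A reader might also infer that a limit on pre-bypass lactate is missing. A cohort that adjusts for baseline lactate needs none. The plan takes "Patients undergoing elective open cardiac surgery with CPB" and excludes emergency surgery, "Presence of any type of preoperative infection (e.g., preoperative pneumonia, infective endocarditis" and similar) and severe hepatic or renal dysfunction, which removes some causes of raised entry lactate.

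**Misclassification.** A patient flat at 2.3 mmol/L throughout bypass might seem wrongly classed. By section 2.4 that patient is exposed, because exposure is the level and not the rise. What is in doubt is the comparison, not the label.

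**The value may already be captured.** Section 2.11.1 lists intraoperative blood gas lactate without limiting it to bypass, and lists preoperative lactate without a window. The full protocol or CRF may fix the sampling time. This stands as a reason to expect a cheap fix. Capturing a value is not the same as naming it as the covariate, however, and the only window the article states is seven days.

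**The magnitude is assumed.** This stands in full. Other adjusters such as age, comorbidities and surgery type could absorb part of the confounding, and a weaker link between pre-bypass lactate and infection shrinks it.

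**Conclusion.** The point holds as one of incomplete control. Preoperative lactate is rightly in the adjustment set, but its stated timing is too loose for a dynamic variable. The adjusted odds ratio may therefore keep residual confounding by lactate present before bypass.

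The direction is probably away from 1. That rests on pre-bypass lactate raising both TWA lactate and infection risk, and on the recorded baseline measuring it imperfectly. The size cannot be derived from the documents, and the range from the illustration is neither an estimate nor a bound. Because a more timely sample is already part of routine care, the weakness is avoidable in part, and the definition should be changed. A lactate that is not recorded at the time may be impossible to recover later.

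**What to change.** - In section 2.6.3 and the CRF, define the preoperative lactate of the adjustment set as the last recorded value after induction and before bypass. The gas drawn 5 min after intubation is one candidate. Confirm that its lactate is recorded and on which analyser, since section 2.7 states neither.
- Keep the value from up to seven days before surgery as a descriptive variable or as an auxiliary variable in the imputation model.
- Report how many exposed patients were already at or above 2.0 mmol/L at that sample.
- As a sensitivity analysis, repeat the primary model without all patients at or above 2.0 mmol/L at that sample, whichever exposure group they fall in.
- Leave the eligibility criteria as they are.

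**Cost.** One definition, probably one CRF field, and one extra model. No new blood draw is needed if the post-intubation gas yields a recorded lactate. The downside is that this value follows induction, so it is not a pre-anaesthetic baseline. A sample 5 min after intubation also precedes incision, sternotomy and cannulation, so some residual confounding remains and should be listed as a limitation.

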#### Surgical factors

2.6.4

Type of surgery (coronary artery bypass grafting, valve surgery, major vascular surgery, combined surgery and other), surgical duration (min), CPB time (min), aortic cross-clamp time (min), anesthesia duration (min), pH and blood glucose levels (mmol/L) from arterial blood gas analysis from the initiation of cardiopulmonary bypass to the end of surgery, body temperature before surgery, during CPB, and at the end of surgery ( °C), hematocrit during CPB (%), duration of body temperature below 32 °C during CPB (min), norepinephrine-equivalent dose (NEE) from the end of CPB to the end of surgery, calculated as NEE = norepinephrine + epinephrine + dopamine/100 + methoxamine/8 + vasopressin×2.5 + ephedrine/10, in µg/kg (35).

### Anesthesia management

2.7

All patients undergoing general anesthesia for elective cardiovascular surgery must receive a standardized preoperative assessment conducted by a multidisciplinary team. Patients with multiple comorbidities or poor baseline status need an individualized perioperative management plan to optimize preoperative condition, reduce surgical risk, ensure procedural safety, and accelerate recovery. Upon admission, the surgeon performs a comprehensive physical examination and formulates the surgical plan. The surgical team and nurses collect the patient's medical history, including prior diseases, surgical experiences, medications, and lifestyle factors. Preoperative laboratory and imaging examinations are completed to assess overall health, including cardiopulmonary evaluation (e.g., electrocardiogram, pulmonary function tests, echocardiography, coronary angiography) and laboratory tests (e.g., blood counts, biochemical markers, coagulation profile, infection-related biomarkers, liver and renal function, myocardial infarction markers).

All patients fast and abstain from fluids for 10 h preoperatively and receive prophylactic antibiotics at least 40 min before surgery. Patients without cephalosporin allergy receive 2 g cefazolin preoperatively; if the surgery lasts over 3 h, an additional 2 g cefazolin is administered. Cephalosporin-allergic patients may receive 1 g clindamycin intravenously. One hour before surgery, 5 mg subcutaneous morphine is administered for preoperative analgesia. Upon entering the operating room, patients are monitored with five-lead ECG, pulse oximetry, and noninvasive blood pressure. Pure oxygen at 6 L/min is delivered via mask, and an 18G peripheral venous line is established.

After local infiltration with 10 mg lidocaine above the left radial artery, the radial artery is cannulated for invasive arterial blood pressure monitoring. Anesthesia induction is performed with the patient in a head-up ramp position: inhalation of pure oxygen at 6 L/min via mask, followed by slow intravenous injection of 0.4 μg/kg sufentanil citrate. After 3 min, 0.3 mg/kg etomidate is administered. Upon loss of consciousness (MOAA/S score of 0), 0.2 mg/kg cisatracurium is given, and endotracheal intubation is performed when the train-of-four count reaches 0. The tube is secured at the right corner of the mouth, and mechanical ventilation is initiated. Arterial blood gas is measured 5 min after intubation, adjusting tidal volume to maintain PaO_2_ 100–200 mmHg and PCO_2_ 35–45 mmHg based on the P_ET_CO_2_–PaCO_2_ gradient. Anesthesia is maintained with propofol 2 mg/kg·h, dexmedetomidine 0.5 μg/kg·h, cisatracurium 0.15 mg/kg·h, and inhaled 1% sevoflurane. Nasopharyngeal and rectal temperature probes and a urinary catheter are placed. Central venous catheterization is performed in a head-left, Trendelenburg position (<45° tilt) for pressure monitoring.

During skin incision, sternotomy, aortic manipulation such as side-wall clamping or aortic cannulation, CPB initiation, rewarming, hemostasis, and sternal wire closure, sufentanil 0.05–0.1 μg/kg is administered. Arterial pressure is maintained at 80–100 mmHg before arterial cannulation for CPB. Heparin 3 mg/kg is given, and ACT is measured 5 min later; arterial cannulation proceeds when the average ACT ≥360 s, and CPB starts when ACT ≥480 s. After CPB initiation, intravenous fluids are stopped or limited to anesthetic maintenance drugs, and CVP is reduced to near 0 or negative. Ventilation is paused after superior and inferior vena cava clamping, and the expiratory valve is set at 5–10 cmH_2_O for static lung inflation. Rewarming during CPB is performed with vasopressor infusion to achieve effective drug concentration before CPB reduction and reperfusion; low-weight or malnourished patients are rewarmed slowly to nasopharyngeal temperature ≥37.0 °C and rectal or bladder temperature ≥36.5 °C before CPB termination, with active warming to prevent hypothermia-induced coagulopathy.

Before opening the ascending aorta, manual high-tidal-volume ventilation (12–15 mL/kg) is applied in a head-down position to expel air from the heart chambers, coordinated with CPB venous drainage. After vena cava release, mechanical ventilation is resumed to match pulmonary blood flow, and tidal volume and respiratory rate are gradually increased before CPB termination based on P_ET_CO_2_.

After CPB, mechanical ventilation is reassessed, CPB fluid balance and pharmacologic interventions (e.g., furosemide, amiodarone) are reviewed, and protamine is administered to neutralize residual heparin (protamine: heparin ratio 1.5–2.5:1) while monitoring airway pressure, blood pressure, heart rate, CVP, and cardiac function. ACT and arterial blood gas are measured 3 min after protamine completion to guide additional dosing. The FiO₂ is adjusted based on the oxygenation index to maintain PaO₂ at 100–200 mmHg.

At the end of surgery, the anesthesiologist, surgeon, and circulating nurse transfer the patient to the cardiac ICU, providing detailed handover regarding intraoperative events, medication usage, pump-drug concentrations, unresolved issues, and total fluid balance, with documentation and signatures.

